### Assessing capacity and obtaining informed consent

The participant must personally sign and date the latest approved version of the Informed Consent Form. This will then be countersigned by a delegated member of the research team before any trial-specific procedures are performed. Written and verbal versions of the PIS will be presented to the participants detailing the trial rationale; participant involvement and responsibilities; the implications and constraints of the protocol; safeguards and processing of blood tests. It will be clearly stated that the participant is free to withdraw from the trial at any time for any reason without prejudice to future care, and with no obligation to give the reason for withdrawal. The member of the research team who takes consent will be delegated to do so, be familiar with the study and be suitably qualified to obtain consent for research purposes. A copy of the signed informed consent will be given to the participant, and another will be stored at the Norfolk and Norwich University Hospital Clinical Research Trials Unit (CRTU). The original signed form will be retained in the patient’s medical records.

### Allocation into study arms

Allocation is based on the patient’s MoCA score, interpreted in the following manner:Score ≥26 indicates normal cognition, with this score being chosen to maximise the sensitivity of the test for detecting early cognitive decline.Score 20–25 suggests early cognitive decline.^24 25^
Score ≤17 suggests possibility of dementia.^28^

### Normal cognition (MoCA score ≥26)

Patients with normal cognition will be informed of their result and will continue to receive usual care by their clinicians. They will be asked to confirm their willingness to continue to participate in the observational study (group O) and will be followed up at 12 months.

### Intermediate stage (MoCA score 20–25)

Patients will be informed of their result and asked to confirm their willingness to continue to participate in the feasibility trial. They will be randomised into one of two groups: control arm (group C) or intervention arm (group I). Randomisation will be based on computer-generated blocked randomisation managed by the Norwich CRTU.

Patients in group C will receive usual care by their clinicians and will be followed up at 12 months.

Patients in group I will undergo enhanced VRF management through assessment by the study team at 3, 6 and 9 months. Specific aims will be set for each modifiable risk factor and the GP will be informed about these targets and the results of each visit.

### Greater degree of cognitive decline (MoCA score <20)

In view of the greater extent of cognitive impairment continued participation in the study is not suitable for these patients. They will be referred to specialist services where relevant, and their GP will be informed.

### Interventions to be measured

#### Blood pressure

Existing evidence demonstrates that lowering of BP consistently and continuously reduces cardiovascular risk. This is supported by the Royal College of Physicians (RCP) guidelines’ aim for BP <140/90 mm Hg, with an ideal target BP <130/80 mm Hg for secondary prevention.^29^ The effect of intervention on BP reduction using 24-hour BP measurement at the beginning and end of the study will be examined. This will be recorded using a SpaceLabs 90 207 monitor programmed to measure BP at 20 min intervals during the daytime (07:00–22:00 hours) and hourly overnight (22:00–07:00 hours).

### Plasma lipids

The link between total cholesterol and dementia is controversial, but from a cardiovascular risk factor point of view lowering cholesterol by using statins improves stroke secondary prevention. Although poststroke dementia can be of VaD type, Alzheimer’s dementia or mixed pathology, lowering cholesterol should contribute to a reduced risk of poststroke dementia where the mechanism is one of VaD. Therefore, the cholesterol aim has been chosen as one of the ‘treat-to-target’ interventions. The total cholesterol aim will be <4.0 mmol/L, which is in line with the RCP guidelines which were current at the trial inception.^29^

### Atrial fibrillation

It has been shown that people with stroke and AF are more likely to be subsequently diagnosed with dementia.^3 5^ An intervention rate aim of 60–80 beats per minute has been chosen for patients with AF; those on warfarin will aim for an international normalised ratio (INR) between 2.5 and 3 to maintain levels in the therapeutic window. There are no specific drug monitoring targets for other anticoagulants.

Ten minutes of continuous beat-to-beat BP measurement will be carried out at baseline and the final follow-up using a Finometer device. These data can be used to assess heart rate variability as well as BP variability.

### Blood glucose

Diabetes mellitus is associated with both microvascular and macrovascular disease, and hence carotid artery disease which is a preventable risk factor for stroke. It has been well documented that poor glucose control (assessed using haemoglobin A1c (HbA1c)) predicts stroke risk.^30^ Therefore, good diabetes control may prevent further cardiovascular risk and be associated with added benefit to future cognitive status. The aim is for HbA1c of 48–53 mmol/mol (or 6.5%–7%).

The patient’s GP will be informed by letter of the results that have been recorded during the research study. All patients will receive standard lifestyle advice relating to diet and weight, smoking and alcohol consumption.

### Ordering of assessments

The following assessments will be carried out on all participants at baseline (table 1):Eligibility assessment and informed consent;MoCA;Demographics, including age, gender, body mass index, smoking status, alcohol consumption and exercise habits;Assessment of past medical history, including VRF;Record concomitant medications.

**Table 1 T1:** Summary of study procedures

Procedures for all participants	Visits					
	Screening	Baseline	3 months	6 months	9 months	12 months
Eligibility assessment	✓	✓	–	–	–	✓
Informed consent	✓	✓	–	–	–	–
Montreal Cognitive Assessment	✓	–	–	–	–	✓
Medical history	✓	–	–	–	–	–
Demographics	–	✓	–	–	–	–
Concomitant medications	–	✓	–	–	–	✓
Physical examination including VRFs	–	✓	–	–	–	✓
Blood sample for cholesterol±INR and blood glucose/HbA1c	–	✓	–	–	–	✓
Adverse events	–	–	–	–	–	✓
Additional procedures for participants in group C						
24-hour BP measurement	–	✓	–	–	–	✓
Beat-to-beat BP measurement	–	✓	–	–	–	✓
Pulse wave velocity measurement	–	✓	–	–	–	✓
Quality of life and functional assessment*	–	✓	–	–	–	✓
Resource use questionnaires	–	✓	–	–	–	✓
Additional procedures for participants in group I						
Eligibility assessment	–	–	✓	✓	✓	–
Assessment of VRFs	–	–	✓	✓	✓	v
Blood sample for cholesterol±INR and blood glucose/HbA1c	–	–	✓	✓	✓	–
Concomitant medications and adherence	–	–	✓	✓	✓	–
Quality of life and functional assessment*	–	✓	–	–	–	✓
Resource use questionnaires	–	✓	–	–	–	✓
24-hour BP measurement	–	✓	–	–	–	✓
Beat-to-beat BP measurement	–	✓	–	–	–	✓
Pulse wave velocity measurement	–	✓	–	–	–	✓
Adverse events	–	–	✓	✓	✓	–

*Includes EQ5D, Dementia Quality of Life measure, Geriatric Depression Scale, Bristol Activities of Daily Living, Morisky Medication Score.

BP, blood pressure; HbA1c, haemoglobin A1c; VRF, vascular risk factor.

In addition, participants in groups C and I will complete at baseline:EQ5D (a generic health-related quality of life questionnaire), DEMQOL (Dementia Quality of Life measure), GDS (Geriatric Depression Scale questionnaire), Bristol Activities of Daily Living questionnaire and Morisky Medication Adherence Score;Resource use questionnaires;BP variability measures including 10 min of continuous beat-to-beat BP recording and 24-hour BP monitoring;Pulse wave velocity (PWV) measurements (which reflect arterial stiffness).

Participants in group I will be seen at 3, 6 and 9 months at which time they will have assessment of their VRF and data collection for adverse events, including recurrent stroke/TIA.

All participants will be followed up at 12 months at which time they will have:MoCA;Assessment of VRF;Recording of concomitant medications;Data collection for adverse events, including recurrent stroke/TIA.

In addition, participants in group C and I will complete at 12 months:EQ5D, DEMQOL, GDS, Bristol Activities of Daily Living questionnaire and Morisky Medication Adherence Score;Resource use questionnaires;BP variability measures;PWV measurements.

### Outcome measurements

#### Primary outcome measure

Recruitment and retention rates at 12 months from the screening and study management logs.

#### Secondary outcome measures

Difference in mean change in MoCA score between groups C and I at 12 months;Proportions of participants in each group whose vascular risk factors are controlled at each time point;Frequency of adverse events in each group;Indicative incremental cost per MoCA point and quality-adjusted life-year (QALY) gained by the intervention;Mean change in MoCA score in group O related to number of VRF and proportion of participants whose VRF are controlled at baseline and outcome.

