### Study objectives

The primary objective of the study is to determine the feasibility of randomising patients who have signs of early cognitive decline, but no dementia, into routine risk factor management or enhanced risk factor management by their GP, and to assess adherence to the proposed intervention by enrolled participants.

The secondary objectives are as follows:Determine the potential clinical benefit of enhanced control of VRF in preventing progression of cognitive decline and the development of dementia poststroke/TIA.Assess indicative cost-effectiveness of this intervention.Estimate the sample size for a future definitive multicentre randomised controlled trial.Identify any adverse events due to the intervention, including rates of recurrent stroke/TIA.Explore the incidence of cognitive impairment on longitudinal follow-up in a UK population after stroke/TIA with current routine risk factor management.

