### Identification of participants

Eligible patients will be given a detailed Patient Information Sheet (PIS) and Consent Form for consideration. After 24 hours the study team will contact the patient again and those who agree to participate will provide written informed consent and undergo a simple and validated cognitive screening test (MoCA), unless this has already been carried out by the clinical team as part of their routine care, whereupon that score can be used for study purposes. If a MoCA has been administered by the TIA clinic team the patient will be given a PIS in clinic and be followed up by phone to discuss entry into the study. Patients who have previously attended stroke services may be screened retrospectively from the Capture TIA/Stroke hospital database and followed up by phone. Those who have a MoCA score ≥26 and who verbally consent to be contacted about the study are sent a study summary sheet, a study invitation letter and consent form. If they wish to participate, the completed consent form will be returned and countersigned by a delegated member of the study team. Those who do not have a MoCA score following their stroke or TIA are invited for an appointment to give consent to take part in the study and carry out the MoCA. The patient will be enrolled into the appropriate arm of the study depending on the MoCA score.

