#### Secondary objectives

Rates of control of VRF at baseline and outcome in each group.Proportion of participants in group I achieving VRF targets at 3, 6 and 9 months for each risk factor.Difference in mean change in MoCA score between groups C and I. The between-group comparison will be based on a general linear model with group as a fixed effect and including any prognostic variables at baseline for which there is a between-group disparity. A 95% CI for the difference in means will be constructed to give an idea of the likely magnitude of benefit from the intervention.Indicative incremental cost per point gained in MoCA, DEMQOL and per QALY gained between groups C and I. Data will be analysed in terms of costs and effects for the two groups. We will analyse key drivers of costs and examine the potential of this intervention to be cost-effective.Change in MoCA score between baseline and 12 months in group O participants, and in groups O and C combined.Difference in adverse event rates between groups.Difference in mean BP between groups C and I.Difference in BP (systolic and diastolic) variability between groups C and I.Difference in PWV between groups C and I.

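### Group O's MoCA change is measured from the same score that selected the group, so it contains a downward regression-to-the-mean component; the planned O+C set should carry the natural-history result

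*Protocol article*

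**What the plan says.** Selection rests on one cognitive score. Under Identification of participants: "The patient will be enrolled into the appropriate arm of the study depending on the MoCA score". If the clinical team has already done a MoCA, the same section allows it to stand, "whereupon that score can be used for study purposes". Under Allocation into study arms: "Score ≥26 indicates normal cognition, with this score being chosen to maximise the sensitivity of the test for detecting early cognitive decline". Patients at 26 or more form the observational group O, those at 20–25 are randomised to C or I, and those below 20 leave the study.

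Table 1 ticks the MoCA at screening and at 12 months and shows a dash at the baseline visit. The text under Ordering of assessments does list the MoCA among baseline assessments, but nothing describes a second test before follow-up.

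The results that depend on this score are:
- the secondary outcome "Mean change in MoCA score in group O related to number of VRF";
- the planned analysis "Change in MoCA score between baseline and 12 months in group O participants, and in groups O and C combined";
- the objective "Explore the incidence of cognitive impairment on longitudinal follow-up in a UK population after stroke/TIA with current routine risk factor management".

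Study overview adds that the combined C and O data should help gauge the size of effect for a future trial. The only model described, a general linear model, is for C versus I.

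**The concern.** A group chosen for being above a cut-off on an imperfectly repeatable test includes some patients whose score was high by chance. On retest their average falls even if nobody has changed. Group C, chosen from 20–25, moves upward for the same reason. A change score that starts from the selecting test cannot separate this from real decline.

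The observational arm was added to supply UK data on cognition after stroke or TIA and its link with vascular risk factors (VRF). If group O is read alone, part of its apparent decline, and of any count of new impairment based on the cut-off of 26, would come from the allocation rule. If patients with more VRF also have lower underlying scores, more of them sit just above the cut-off and regress further, which can imitate a VRF effect.

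**Working it through.** The article gives no expected change for group O, no MoCA SD and no reliability, so there is no planned figure to reproduce.

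**Inputs from the article.** Cut-off 26; group C from 20–25; about 100 patients in O and 50 in C; prevalence of cognitive impairment at diagnosis about 30% (Sample size calculation). That prevalence is not defined there as MoCA below 26, so the 70% row below is a calibration, not a fact.

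**Assumed.** SD of screening scores 3–4; retest reliability r 0.7–0.9; 50–70% of those screened scoring 26 or more; no true change. The scale maximum is taken as 30.

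**Closed form, ignoring the ceiling.** Let p be the share scoring 26 or more, and a the standard normal point with upper tail p. Expected change in O = −(1−r) × SD × φ(a)/p.
- p = 0.70: φ(a)/p = 0.348/0.70 = 0.497. SD 3, r 0.9: −0.1 × 3 × 0.497 = −0.15. SD 4, r 0.7: −0.3 × 4 × 0.497 = −0.60.
- p = 0.50: φ(a)/p = 0.399/0.50 = 0.798. SD 4, r 0.7: −0.3 × 4 × 0.798 = −0.96.

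**Simulation** (1,000,000 patients per setting, scores rounded and capped at 30) agrees. Repeat runs differ by about 0.01.

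| Share ≥26 | Group O change | O below 26 at retest | O+C, unweighted 100:50 | O+C, weighted to screening shares |
|---|---|---|---|---|
| 70% | −0.16 to −0.59 | 9–16% | +0.01 to +0.04 | −0.01 to −0.06 |
| 50% | up to −0.96 | up to 25% | down to −0.39 | down to −0.17 |

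Group C rises by 0.24 to 1.26 across these settings.

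**How pooling works.** In the worst setting O changes by −0.95 and C by +0.73.
- Unweighted: (100 × −0.95 + 50 × 0.73)/150 = −0.39.
- Weighted: (0.50 × −0.95 + 0.433 × 0.73)/0.933 = −0.17.

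At 70%, with SD 3 and r 0.7, unweighted pooling gives (100 × −0.46 + 50 × 1.03)/150 = +0.04. Weighting gains nothing there, because 100:50 is already close to 70:30.

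**Crossing the cut-off.** With 50% at 26 or more, SD 3 and r 0.7, about 127 per 1,000 screened fall below 26 and about 126 rise from 20–25 to 26 or more. One-way counting sees only the first group.

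**VRF gradient.** Suppose, as an assumption, that high- and low-VRF patients have screened means of 25 and 26.5 (SD 3, r 0.8). In group O alone the spurious change is −0.57 v −0.38, and 23% v 15% fall below 26. With O and C in their screening shares the change is −0.05 v −0.02. In a 100:50 sample with equal VRF halves, O splits 40.8:59.2 and C 29.8:20.2, and C changes by +0.38 and +0.61:
- high VRF: (40.8 × −0.57 + 29.8 × 0.38)/70.6 = −0.17;
- low VRF: (59.2 × −0.38 + 20.2 × 0.61)/79.4 = −0.13.

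The gap shrinks from about 0.2 to 0.04 points.

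**The case against.** The strongest reply is that the protocol already plans the O+C analysis, in which the opposite movements largely cancel. This stands for the mean: over the assumed range the unweighted pool is within −0.39 to +0.04, so weighting is a refinement. It does not rescue the outcome named for group O alone, and the VRF question is attached to that outcome.

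Second, the net change need not be negative. The Rationale notes that decline after TIA or minor stroke may be transient, and practice raises retest scores. This also stands. With SD 3, r 0.8 and screened means of 25–26, a 0.5-point gain leaves −0.14 to −0.03 and a 1-point gain gives a net rise. Even so, 12–17% and 8–11% respectively would still fall below 26. A reader might infer that group O is bound to show a decline; the documents do not support that.

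Third, a reader might infer that 9 to 25 false incident cases will be reported. The article nowhere defines incidence as crossing from 26 or more to below 26; these counts apply only if it is measured that way.

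Fourth, the VRF gradient is conditional and small. With a change SD of about 1.7 and 50 v 50 patients, the standard error is 1.7 × √(2/50) = 0.34, larger than the assumed gap of about 0.2.

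Fifth, weighting and modelling details normally belong in a statistical analysis plan, which is not shown. That is fair for the details, but the article itself fixes the group O change score as an outcome.

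Blinding of the 12-month assessor does not help: it guards against assessor bias, not regression to the mean.

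**Conclusion.** The point holds within limits. One screening MoCA both selects group O and serves as its baseline, so the group's raw mean change, and any incidence counted as falling below 26, contain a downward component. That direction follows from the design. The size depends on assumed SD, reliability and score distribution, with the range shown in the table; the upper figures need only half of those screened to score 26 or more.

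Two stronger readings fail. The randomised C versus I comparison is not biased, since both arms are selected alike from 20–25. The natural-history data are not unusable either, since the planned pooling removes most of the bias in the mean over the assumed range. The primary outcome, recruitment and retention, is untouched. This is a correction to an exploratory secondary outcome of a feasibility study, worth making because the protocol intends the combined data to inform a future trial.

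**What to change.** Amend Secondary outcome measures and the Secondary objectives part of the Data analysis plan as follows.

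1. Make the already planned O+C set the main natural-history estimate, and fit the associations between VRF and MoCA change in that set.
2. Report group O alone only beside the change expected from regression to the mean, over a stated range of reliability.
3. If incidence is reported as crossing 26, show the reverse crossing, from 20–25 to 26 or more, in group C beside it. The difference between the two describes change in prevalence, not incidence, and should be labelled so.
4. As a sensitivity analysis, weight O and C to their proportions in the screening log. State its limits: some patients were screened retrospectively from a database, so log proportions may not represent the population, and scores below 20 are excluded, so the regression cannot cancel fully.

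A second MoCA after selection would have removed the component (in simulation −0.57 becomes 0.00), but recruitment ended in July 2017, so the remedy has to be analytic. The data needed are already collected, and screening logs are kept for the primary outcome. The cost is a little more analysis, a slightly wider interval when weighted, and a less striking decline in group O.

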### Sample size calculation

As this is a feasibility study a formal sample size calculation has not been performed. The duration and sample size of the study are based on the estimated prevalence rate of cognitive impairment at diagnosis (around 30%),^4^ incidence of dementia after the event (~30% in 3 months),^3^ estimated screening and recruitment rates. The aim is to include a minimum of 100 patients in the feasibility study (50 per group) and another 100 patients in the observational study.

### Data analysis plan

#### Primary objective

Proportion of participants with MoCA score 20–25 who consent to join the trial.Adherence to follow-up, including rates of withdrawal and loss to follow-up.Number of risk factors that need to be targeted in these patients administering the client service receipt inventory (CSRI) and quality of life questionnaires. Originally designed for costing psychiatric interventions, the CSRI^31^ has been used as the core resource use measurement tool for a wide variety of interventions. It requires adapting to fit each study question, therefore the feasibility study will allow testing and revising of the questionnaire in preparation for the full study.

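### The primary recruitment proportion cannot count patients who refuse before they are tested, so it overstates willingness by an amount that depends on the route of recruitment

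*Protocol article*

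**What the plan says.** Under Data analysis plan, Primary objective, the protocol article lists as its first item the "Proportion of participants with MoCA score 20–25 who consent to join the trial". Under Primary outcome measure it names "Recruitment and retention rates at 12 months from the screening and study management logs", without a denominator. The analysis item is therefore the only definition of a recruitment proportion that the article gives.

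The order of consent and testing is set under Identification of participants. By default, "those who agree to participate will provide written informed consent and undergo a simple and validated cognitive screening test (MoCA". There is an exception for a MoCA already on record: "unless this has already been carried out by the clinical team as part of their routine care, whereupon that score can be used for study". The TIA clinic has a similar route: "If a MoCA has been administered by the TIA clinic team the patient will be given a PIS in clinic". For retrospectively identified patients without a score, consent again comes first: "Those who do not have a MoCA score following their stroke or TIA are invited for an appointment to give consent", and the MoCA follows. The section on capacity and consent makes the order general; of the signed form it says "This will then be countersigned by a delegated member of the research team before any trial-specific procedures are performed".

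A second decision follows the test. Under Intermediate stage, patients scoring 20–25 are told the result and "asked to confirm their willingness to continue to participate in the feasibility trial" before they are randomised.

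**The concern.** A patient can belong to the group scoring 20–25 only if a score exists. On the consent-first routes a score exists only for people who have already agreed to take part. Those who turn the study down at first approach are missing from both numerator and denominator, and what is left is the rate at which people who have already consented agree to carry on.

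On the prior-MoCA routes the score is known before the approach, so a refuser with 20–25 can be counted. Pooling the routes gives a figure that depends on how often the local clinical team happens to test before the study team makes contact. That share may well differ at other hospitals.

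Feasibility of recruitment is the primary objective, and the study is meant to inform a definitive multicentre trial. A recruitment proportion that leaves out some refusals can only err on the favourable side, and it would suggest that fewer patients need to be approached than is the case.

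**Working it through.** The article states no acceptance rate, so there is no figure of its own to reproduce. The check sets the routes side by side and then uses a simple flow model.

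**Routes into the randomised trial**

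| Route | Order | Are refusers at first approach with MoCA 20–25 countable? |
|---|---|---|
| Default | consent, then MoCA | No |
| Retrospective, no MoCA on record | consent, then MoCA | No |
| MoCA done in routine care | MoCA, then consent | Yes |
| MoCA done by the TIA clinic team | MoCA, then consent | Yes |

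The article gives no share of patients for any route. For database patients with a known score it describes a procedure only for scores of 26 or more, which lead to the observational group.

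**Model.** Take all approached patients who score, or would score, 20–25.

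- c = proportion who consent at first approach (assumed; not in the article)
- k = proportion of those who confirm after the result (assumed; not in the article)
- f = share whose MoCA was known before consent (not in the article; varied from 0 to 1)

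For simplicity, c and k are taken to be the same on all routes and unrelated to the score.

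- True acceptance = c × k
- Denominator of the stated measure = f + (1 − f) × c, because consent-first refusers drop out
- Stated measure = c × k ÷ [f + (1 − f) × c]
- Overstatement factor = 1 ÷ [f + (1 − f) × c]

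**Example with c = 0.5 and k = 0.9.** True acceptance = 0.5 × 0.9 = 45%.

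| f | Denominator | Stated measure | MoCA 20–25 patients to approach for 100 randomised, as implied by the measure |
|---|---|---|---|
| 0 | 0.500 | 0.45 ÷ 0.500 = 90% | 111 |
| 0.25 | 0.625 | 0.45 ÷ 0.625 = 72% | 139 |
| 0.5 | 0.750 | 0.45 ÷ 0.750 = 60% | 167 |
| 0.75 | 0.875 | 0.45 ÷ 0.875 = 51% | 194 |
| 1 | 1.000 | 45% | 222 |

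The number truly needed is 100 ÷ 0.45 = 222 throughout. The overstatement factor is 2.0 at f = 0, 1.33 at f = 0.5 and 1.0 at f = 1.

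**Other values of c, with k = 0.9**

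| c | True acceptance | Measure at f = 0 | Measure at f = 0.5 | Measure at f = 1 |
|---|---|---|---|---|
| 0.3 | 27% | 90% | 0.27 ÷ 0.65 = 42% | 27% |
| 0.7 | 63% | 90% | 0.63 ÷ 0.85 = 74% | 63% |

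At f = 0 the measure equals k whatever the value of c, so it carries no information on refusal at first approach. The direction of the error does not rest on the simplifying assumptions: leaving refusers out shrinks the denominator and leaves the numerator as it is.

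**The case against.** The strongest case against has four parts.

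- **Size.** The article does not say how many patients had a MoCA before consent. If nearly all did, the error would be close to nil. This stands. A reader might infer from the default order that most patients were tested only after consent, but no proportions are given and two prior-MoCA routes are described.
- **The measure is not empty.** Patients learn their result and then make a real second decision, and refusals by patients with a prior MoCA can also be counted. This stands too. A reader might infer that the figure must come out near 100% whatever the true willingness. That would need both a high confirmation rate and almost no prior MoCAs, and the article supports neither.
- **The primary outcome is broader than this item.** It refers to recruitment rates from the screening logs, and the article commits to the CONSORT extension for pilot and feasibility trials, so numbers approached may be reported anyway. That makes the repair easy. It does not correct the one proportion that the article defines.
- **A condensed article leaves detail to the full protocol or analysis plan.** This is true of stage-by-stage tables and monthly rates. Here, though, a denominator is stated, and it does not fit the consent order in the same article. The point is therefore not one of missing detail.

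It is also fair to say that the article sets no progression threshold on this proportion and does not use it to project how many patients must be approached. The implied numbers shown in the working are what a later reader could derive from it, not a claim of the plan.

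**Conclusion.** The point holds as a defect in the definition of the first primary-analysis item. For patients without a prior MoCA, refusal at first approach cannot be counted. For patients with one, it can. The pooled proportion therefore mixes two quantities and overstates willingness whenever some patients are tested only after consent and some refuse at first approach. It never understates it for this reason.

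The size cannot be stated from the article. With the assumed 50% first consent and 90% confirmation, the overstatement runs from none (45% reported, 45% true) to a doubling (90% against 45%) as the share with a prior MoCA falls from all to none. A reader might take the upper end as the expected result, but that end requires that no MoCA 20–25 patient had a prior MoCA, which the article does not say.

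**What to change.** Report the following separately from the screening logs:

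- (a) first consent among all eligible patients approached;
- (b) the share of those tested who score 20–25;
- (c) confirmation and randomisation among those scoring 20–25, split by whether the MoCA preceded consent.

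For the consent-first route, take overall acceptance as (a) × (c), using the figures for that route, and state the assumption that first consent does not depend on the MoCA score. For the prior-MoCA route, use the direct proportion randomised among all those approached who score 20–25.

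Give randomised ÷ approached as a recruitment yield for planning the later trial, not as an acceptance rate. It counts patients scoring 26 or more, who go to the observational group, and those below 20, who leave the study, as if they had not been recruited.

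The cost is a change of wording, a small amount of extra tabulation and a less favourable reported rate. Recruitment ended in July 2017, so the change is possible only if the logs recorded refusals at first approach. If they did not, the reported proportion should be described as confirmation among those tested, with the limitation stated.
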